##### Educational Intervention 

The educational intervention is scheduled at the university headquarters (residential event(s), experiential workshop), the NH site (on-site training), and online (asynchronous self-learning activities and potentially a community of practice) and will start within a month since the baseline assessment. It will unfold during the study. For details, see the paragraph Intervention set up. 

##### Follow-Up Assessment (T1, T2)

HCPs and family carers will complete the paper questionnaires at 4 weeks (T1) and 6 months (T2) since the first learning module (assessment time of about 10 and 15 min for HCPs and family carers, respectively). The reference person will collect data from clinical records about any hospital services used by residents with associated reasons and any ACP documents in place (assessment time of approximately 10 min). 

##### Outcome Measures 

A range of measures will be collected to capture the effect of the *Teach-to-communicate* training program at multiple levels:

Family carers: quality of communication, burden, quality of care, satisfaction with the care received;

HCPs: quality of communication, confidence in and obstacles to serious illness conversations;

Residents: completion of any ACP documents.

The primary outcome is the quality of communication perceived by family carers at T2. Outcomes with their assessment tools are reported in Table 2. 

##### Quality of communication

We will assess the quality of communication considering two perspectives: HCPs and family carers. At T0, T1, and T2, family carers will complete the family carer version of the QOC questionnaire [36] and HCPs the HCP version. The family carer/patient version of the QOC was developed using quantitative and qualitative methods and is available in two versions (17-item and 13-item). In this study, we will use an adaptation of the 13-item version measuring general communication (six items) and communication about end-of-life care (seven items), each rated on a scale from 0 (“very worst I can imagine”) to 10 (“very best I can imagine”) or identified as something the HCP did not do (“did not do”) or that family carers were unsure of how to rate the HCP on a particular skill (“don’t know”). The 0/10 ratings are recoded to 1/11, with 0 imputed for “did not do”. 

In addition to the QOC, family carers will report self-perceived communication quality on a scale from 0 (“very worst”) to 10 (“very bad”). 

The HCP version of the QOC consists of two items exploring the confidence of HCPs in talking about dying and the quality of communication they perceive to provide, each rated on a scale from 0 (“at all/very worst”) to 10 (“extremely comfortable/very best”). “Don’t know” option is available. 

##### Other Outcome Measures 

Family satisfaction with care at the end of life will be assessed using the SWC-EOLD. This consists of 10 items (α = 0.90) and each scored on a 4-point Likert scale [37]. Moreover, we will assess overall satisfaction with care, satisfaction with medical care, and nursing care on a 5-point Likert scale ranging from “at all” to “very much”.

Family carers burden will be assessed using the ZBI [46], a 22-item self-report measure of subjective burden among family carers that addresses functional and behavioral impairments as well as the home care circumstances. In this study, we will remove items 11 and 13 since they specifically refer to the care home environment and, therefore, they are not applicable to the NH setting. Each item was scored on a 5-point Likert scale ranging from 0 (never) to 4 (nearly always present). Therefore, a 20-item tool with a total score of 0 (low burden) to 80 (high burden) will be used. 

Family carers’ self-reported care quality and HCPs’ confidence in communication will be assessed on a 5-point Likert scale ranging from “at all” to “very much”.

Semi-structured ad hoc questionnaires will be employed to assess hospital services used by residents, with their associated reasons, and any ACP documents.

Semi-structured interviews with both HCPs and family carers will inform on the intervention quality, its implementation barriers, and suggestions for improvement (for details, see the paragraph nested qualitative study).

##### Kick off and over-the-Project Meetings

There will be three study meetings based on remote modalities (video calls): the kick-off meeting will be held before baseline data collection (T0) starts. Participants will be two members of the research group, the NH managers, and the reference persons responsible for data collection in each facility. The purpose of this meeting is to provide clear information on the objective and procedure and to guide participants through the study documentation. The second meeting will be held the week before T1 data collection to discuss possible doubts, top-up the motivation of NHs, and provide a safe place for peer discussion on the implementation of the intervention. The third meeting will take place the week before T2 data collection to refresh the study aim, discuss possible difficulties that arise, and reflect on potential solutions. All meetings will last about 1.5–2 h. Additional meetings will be organized according to the needs of each NH. In addition, a reference person from the research team will be available for inquiries. 

**(iii)** 
**Nested qualitative study (T3)**

Eight weeks after the T2 follow-up assessment, family carers and HCPs involved in the *Teach-to-Communicate* training program will be involved in one-on-one, semi-structured, face-to-face or remote-based interviews according to their preferences (T3). The T2 questionnaire for both family carers and HCPs will ask for their willingness to be interviewed along with a reference contact (email or telephone). Interviewees will be identified using a maximum variation strategy. A minimum of 10 interviews with family carers and 10 interviews with HCPs will be held; the final number will depend on the achievement of “data saturation” [47]. 

The interviews will work as a process measure by informing participant perceptions of the quality of the training program, its impact, and its refinement. They will last no more than one hour and be led by members of the research team trained in qualitative research and not involved in the *Teach-to-Communicate* training program to reduce social desirability response bias. Open-ended questions with probes (e.g., what, which, why, how) will be employed to achieve an in-depth understanding of the experience and body language noted. Participants will be reassured that interviews are confidential and will be anonymized; moreover, information about the purpose of the study and the opportunity to stop the interview at any time and for any reason will be provided and written consent will be obtained. Before ending the interview, participants will have the opportunity to add any further thoughts or reflections. 

The interview with family carers aims to explore the quality of communication with HCPs in the last two months, perceived changes in the quality of communication, and/or the quality of care provided to the relative after the NH adhered to the project. The interview with HCPs will involve the HCPs engaged in the *Teach-to-Communicate* training program and is aimed at collecting lived experiences about the intervention and its impact on the quality of communication with family carers, possible barriers and facilitators to implementation, and suggestions for changes to ameliorate the intervention. 

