**(ii)** 
**Pilot pre-post study**

Four NHs will be purposefully involved in the pilot feasibility pre-post study and sampled for geographical area and size to ensure the greatest variation of data. All NHs will be located in the northwest of Italy and will participate on a voluntary basis. Participation will be promoted through a local nursing home association network. 

There will be a baseline assessment (T0), the beginning of the training program within 1 month of the baseline assessment, and a follow-up assessment within 4 weeks of the initiation of the training program (T1) and 6 months (T2) thereafter. The baseline and follow-up assessments will be performed via anonymized records filled in by paper and pencil. A member of the research team will input the collected data into a password-protected database accessible only to the team members.

Participants (NH staff, family carers) will be free to withdraw from the study at any time, without giving reasons and without consequence. Information about drop-out reasons will be collected. 

The objectives of the pilot feasibility pre-post study are reported in Box 1. The study procedures are shown in Figure 2.

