##### Baseline Assessment (T0)

A reference person will be identified in each NH. This person will identify eligible HCPs and family carers, provide written information about the purpose and procedures of the study, and obtain signed informed consent forms, according to the Declaration of Helsinki and the Good Clinical Practice guidelines of the EU. The informed consent is kept on file by the study personnel and is available for inspection purposes.

Family carers will be approached when they come to visit their relative, while HCPs will be approached before starting or at the end of their working shift. Family carers and HCPs who adhere to the project will fill in a baseline questionnaire on paper, which will be returned to the reference person. The completion time is about 10 min for the HCP questionnaire and 15 min for the family carer questionnaire. The reference person will collect data from clinical records about any hospital services used by residents in the last month (i.e., type of service, reason(s) for using, and number of day(s)/attendances) and if any ACP documents were in place (i.e., advance care plan, advance decision to refuse treatment, do not hospitalize, do not resuscitate, do not intubate, no artificial feeding, no artificial hydration, no invasive diagnostic procedures, comfort-oriented care, power of attorney). 

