### 2.4. Data Management

All data will be stored on a password-protected computer and a central hard disk from the research team. The data of the participants will be pseudonymized, and only the principal investigator will be able to link raw data to personal data. Data will be stored for a minimum of 5 years after the appearance of publications based on this database. After this period, the data can be destroyed.

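### The T2 questionnaire, which carries the primary outcome, also asks for an email or telephone contact; this conflicts with the stated anonymity and makes T2 more openly self-identifying than T0

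*Protocol article*

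**What the plan says.** On recruitment to the interviews, the Nested qualitative study (T3) section states: "The T2 questionnaire for both family carers and HCPs will ask for their willingness to be interviewed along with a reference contact"; the contact is an email address or telephone number. The descriptions of the T0 and T1 assessments mention no such request.

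On the endpoint, the Outcome Measures section states: "The primary outcome is the quality of communication perceived by family carers at T2".

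On confidentiality, the Pilot pre-post study section states: "The baseline and follow-up assessments will be performed via anonymized records filled in by paper and pencil". It adds that a research team member enters the data into a database open to the team. Section 2.4, Data Management, says something different: "The data of the participants will be pseudonymized, and only the principal investigator will be able to link raw data to personal data".

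On handling of forms, Baseline Assessment (T0) says that consenting carers and HCPs "will fill in a baseline questionnaire on paper, which will be returned to the reference person". That person has also identified the eligible respondents and obtained their signed consent. The section on project meetings refers to "the reference persons responsible for data collection in each facility".

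**The concern.** Two things are at stake.

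The first is confidentiality. Participants are told that their data are confidential (section 4, Ethics and Dissemination). A rating form bearing the respondent's own email or telephone number is neither anonymized nor coded. Whoever handles it sees personal data and ratings together.

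The second is measurement. The study has one arm, and its estimate of effect is the within-carer change from T0 to T2. With no control group, a difference in how the two questionnaires are administered cannot be separated from an effect of training. At T2, a carer rating the staff who look after a relative is also invited to leave a contact and to expect a possible interview. Some may answer more favourably as a result. The plan recognises this type of bias, since it uses interviewers from outside the training program to limit it, but that safeguard covers the interviews and not the T2 rating form.

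**Working it through.** The point rests on reading passages together. No figure in the plan is wrong because of it.

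**Step 1: do the three descriptions of the T2 form agree?**

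| Section | Status of the T2 form |
|---|---|
| Pilot pre-post study | Anonymized, as at baseline; entered by a research team member |
| 2.4 Data Management | Pseudonymized; only the principal investigator can link |
| Nested qualitative study (T3) | Contains a question on interview willingness and a personal contact |

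Anonymized and pseudonymized are different states, so the first two rows already disagree. For a respondent who leaves a contact, the third row contradicts both. The record is not anonymized, and the team member who enters it can make the link without the principal investigator. The homes' reference persons may also see it, because they are responsible for data collection. For a respondent who leaves no contact, only the disagreement between the first two rows remains.

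**Step 2: is T0 anonymous?** No.
- The T0 form goes back to the reference person who enrolled the respondent and took consent (Baseline Assessment).
- Section 2.3.1 plans a paired t-test or Wilcoxon signed-rank test, which requires T0 and T2 forms to be linked within person.
- Section 2.4 provides for a link to personal data without excepting any time point.

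**Step 3: what then differs between T0 and T2?** The degree of open self-identification. At T0 a respondent can be identified through the reference person and the code. At T2, those who agree to be contacted also write their own contact on the questionnaire and expect a possible interview.

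**Step 4: can the effect on the primary outcome be sized?** No. It would need the share of carers who leave a contact, and the shift in their ratings compared with a form without one. The document gives neither, and does not establish the direction. For scale only, section 2.2 plans on a 2-point change on the 13-item QOC; if items are summed this is 2 / 13 = 0.15 point per item.

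**Step 5: is the recruitment target affected?** No. Section 2.2 gives a standardized effect of 0.60, power 0.85, two-sided α of 0.05 and 20% loss. A paired t-test needs 27 evaluable carers. Allowing for the Wilcoxon test at its minimum relative efficiency of 0.864 gives 27 / 0.864 = 31.25, rounded up to 32, and 32 / 0.80 = 40. This matches the stated target of 40, although the plan does not name its method. The contact request enters none of these inputs.

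**The case against.** The strongest reply is that little about identity is new at T2. The reference person already knows who returned the baseline form, and the paired analysis needs linked forms throughout. A telephone number adds almost nothing to what the home knows, and only volunteers supply one. The article shows no forms: it is silent on T0 and T1 rather than saying that no contact is requested, and the T2 item could sit on a detachable last sheet. Only the return route of the baseline form is spelled out. The study is a pilot that lists its single-arm design as a limitation, beside which a contact field is minor.

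Most of this stands, and it limits the point. A reader might infer that ratings are identifiable at T2 but not at T0. The document does not support that, for the reasons in step 2. A reader might also put a number on the bias. For example, if half of carers left a contact and rated each item 0.3 point higher, the mean shift would be 0.5 × 0.3 × 13 = 1.95 points, close to the planned 2. Both inputs are invented, and so is a uniform shift across all items, so the result carries no weight.

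The reply does not remove the conflict of wording. The article places the request in the questionnaire, calls the follow-up records anonymized, and reserves linkage to one person. A detachable sheet would solve this in practice, but the text as written does not provide for one. Pilot status is only a partial answer, because the study is meant to assess potential effectiveness and to inform later sample sizes.

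**Conclusion.** The point holds in a limited form. The contact request on the T2 questionnaire contradicts both the statement that follow-up records are anonymized and the statement that "only the principal investigator will be able to link raw data to personal data", for every respondent who gives a contact. That follows from the text and needs no assumption about bias, except that the contact stays with the ratings, which is how the article describes it.

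The measurement part is weaker. T2 is more openly self-identifying than T0, in a comparison with no control group, so social desirability bias at the primary endpoint is possible. Its size and direction are unknown. It concerns carers who volunteer a contact; for HCPs the same issue touches secondary outcomes only. The sample size is unaffected. The correction is worth making because it is simple and removes both problems.

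**What to change.** 1. Remove the interview-willingness question and the contact field from the T2 outcome questionnaire.
2. Collect them in one of two ways: on a separate reply slip, in its own envelope addressed to the research team and handed out after the T2 form has been returned; or as permission to be contacted, given with consent at T0.
3. State one identification scheme for T0, T1 and T2, namely pseudonymized by study code with no contact detail on any outcome form. Reconcile the Pilot pre-post study section, the Nested qualitative study (T3) section and section 2.4 with it.

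The cost is one extra sheet and envelope per participant if the slip is used, and a few slips may not come back. The sample size and the analysis do not change.

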### 2.2. Study Power

A formal sample size calculation is not required since this is a pilot feasibility study. However, by hypothesizing a 2-point change and moderate effect size (γ = 0.60) on the QOC questionnaire filled in by family carers at T2, with a power of 0.85, 2-sided α = 0.05, and 20% of family carers lost at T2, we aim to recruit at least 40 family carers. The 2-point change on the QOC questionnaire was based on the hypothesis that the intervention would improve at least two QOC items by 1 point [16]. 

### 2.3. Data Analysis

#### 2.3.1. Quantitative Data

Descriptive statistics will be employed. Categorical variables will be summarized as numbers and percentages, while continuous variables will be summarized as mean and standard deviation (SD), or median and interquartile range (IQR). Categorical variables will be compared using the χ^2^. The Shapiro–Wilk test will be adopted to test the normality assumption of continuous variables. Depending on the data distribution, the paired t-test or the Wilcoxon signed-rank test will be carried out; correlations will be computed using Pearson’s or Spearman’s coefficients. As an additional analysis of the temporal change in the primary outcome (i.e., the quality of communication as perceived by family carers), a linear regression analysis using time as a covariate will be used to test for a trend in the quality of communication. As the analysis will be performed at the family carer level, the Huber–White estimator will be used to adjust for the correlation between the multiple observations contributed by the same NH. A significant coefficient of the time variable will indicate that the primary outcome changes with respect to time. The goodness of fit will be evaluated by R^2^.

Change in the secondary outcome measures will be calculated, as well as the following feasibility outcomes: recruitment rate of HCPs engaged in the training program (and reasons for non-enrolment); retention rate (proportion of HCPs completing the training program; proportions of family carers and HCPs completing follow-ups); missing data (proportion fully completed for each scale at each time point). In the case of missing values, multiple imputation will be performed. A p value less than 0.05 will be considered statistically significant. All analyses will be performed using SPSS v. 27. 

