Additionally, the COVID-19 pandemic highlighted the need for specialized training in technology-based communication in addition to in-person interactions [25]. Establishing trusting relationships and building meaningful dialogues in virtual settings may be complex and impeded by several obstacles, including little or limited bodily communication and an increased risk of misunderstanding [26]. Therefore, it is crucial to develop educational initiatives that aim to increase the communication skills of HCPs and their confidence to handle conversations about serious diseases both in person and in remote settings. 

This project aims at setting up and evaluating the feasibility and effectiveness of a blended educational communication skills training, targeted at the HCPs who work in the NH setting, that includes traditional didactic methods and e-learning. The intervention is framed within an innovative pedagogical approach that employs experiential methodologies and integrates the teaching of specific theoretical communication models with the promotion of self-reflection and relational abilities in an interdisciplinary context [27]. Our study hypotheses are that the training program will produce: (a) better quality of communication reported by family carers and HCPs; (b) greater HCPs’ confidence to sustain both in-presence and technology-based serious illness conversations; (c) improved family carers’ satisfaction with the care received; (d) reduced family carers’ psycho-emotional burden; and (e) increased completion of any advance care planning (ACP) documents.

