### Limitations

A single-arm design for the pilot study was employed since interventions to improve the quality of communication in NHs are currently at a premium and designing a randomized trial was judged ethically unviable. Our training program targeted only HCPs; interventions targeting multiple stakeholders (i.e., HCPs, residents, and/or family carers) were suggested to improve the quality of serious illness conversations [paper under revision]. However, in the current Italian situation regarding the communication skills needs of NH staff, we deemed it a priority to focus on enhancing the communication competencies of HCPs [7]. 

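### No paired test is named for binary before-after outcomes, so the ordinary χ² would treat repeated readings of the same residents' advance care planning status as independent samples

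*Protocol article*

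**What the plan says.** The only test that section 2.3.1 (Quantitative Data) of the protocol article gives for categorical data is in one sentence: "Categorical variables will be compared using the χ^2". For continuous data, the same paragraph says that "the paired t-test or the Wilcoxon signed-rank test will be carried out", depending on the distribution. A later sentence says that change in secondary outcomes will be calculated, without assigning a test to any of them. The significance threshold is p < 0.05 throughout.

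The Limitations section says "A single-arm design for the pilot study was employed". The Introduction's hypothesis (e) is "increased completion of any advance care planning (ACP) documents", and the one resident-level entry in the outcome list is "Residents: completion of any ACP documents". The reference person reads the clinical records at baseline to see "if any ACP documents were in place". At T1 and T2 the same person collects "any hospital services used by residents with associated reasons and any ACP documents in place". Table 2 confirms all three time points. The Discussion refers to ACP documentation as a binary outcome.

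**The concern.** With one arm, the only comparison that bears on hypothesis (e) is T0 against T1 or T2, and both readings come from the same residents' records. Pearson's χ² on the two proportions assumes that the T0 and T2 readings are independent. ACP status at T0 will usually predict status at T2, so the true variance of the difference is smaller than the χ² formula assumes.

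At stake is the reading of the one hypothesis that concerns residents. The Discussion says this outcome will show potential effectiveness at patient level. A real rise could be reported as non-significant because the test ignores the pairing that the same paragraph respects for continuous measures.

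**Working it through.** **Inputs from the document.** One arm. ACP status read at T0, T1 and T2. Two-sided α = 0.05. At least 40 family carers recruited and 20% lost at T2 (section 2.2), so 40 × 0.8 = 32 pairs if a resident's T2 record is lost along with the carer. The 40 is set for the primary communication questionnaire. The plan gives no rate, effect or sample size for ACP, so there is no ACP figure to reproduce.

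**Assumed.** The ACP rates and the within-resident correlation φ are assumptions, shown as ranges. Residents are taken as independent of one another.

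**Step 1: why pairing matters.** With proportions p₀ and p₁ on n residents, the variance of the difference is

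[p₀(1−p₀) + p₁(1−p₁) − 2φ√(p₀(1−p₀)p₁(1−p₁))] / n.

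Pearson's χ² leaves out the last term. When p₀ = p₁, the true variance is (1−φ) times the one it uses. At φ = 0.5 it therefore rejects only when |Z| > 1.96/√0.5 = 2.77, a true level of about 0.6%.

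**Step 2: example with 40 residents.** 10 have documents at T0 and 16 at T2; 6 gained, none lost.
- Pearson: pooled proportion 26/80 = 0.325; χ² = 0.15² / (0.325 × 0.675 × 2/40) = 0.0225/0.01097 = 2.05; p = 0.152 (0.233 with continuity correction).
- Exact McNemar, 6 against 0: p = 2 × (1/2)⁶ = 0.031.
- Standard error of the 15-point difference: unpaired √(0.25×0.75/40 + 0.40×0.60/40) = 10.3 points; paired √(6 − 6²/40)/40 = 5.6 points.
- Correlation in this table: φ = (10×24 − 0×6)/√(10×30×16×24) = 0.71.

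**Step 3: example with 32 residents.** 8 at T0 and 15 at T2; 7 gained, none lost.
- Pearson: pooled 23/64 = 0.359; χ² = 0.21875² / (0.359 × 0.641 × 2/32) = 3.33; p = 0.068.
- Exact McNemar, 7 against 0: p = 2 × (1/2)⁷ = 0.016.
- φ = (8×17)/√(8×24×15×17) = 0.61.

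In both examples the two tests fall on opposite sides of 0.05.

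**Step 4: true level when nothing changes.** Exact enumeration of the paired table, 32 pairs, 30% at both visits:

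| φ | Pearson χ² | McNemar, asymptotic | McNemar, exact |
|---|---|---|---|
| 0 | 0.052 | 0.045 | 0.026 |
| 0.3 | 0.021 | 0.043 | 0.022 |
| 0.5 | 0.007 | 0.047 | 0.015 |
| 0.7 | 0.001 | 0.043 | 0.005 |

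**Step 5: power for a rise from 20% to 40%.**

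| Pairs | Correlation | Pearson χ² | McNemar, asymptotic | McNemar, exact |
|---|---|---|---|---|
| 32 | φ = 0.3 | 0.41 | 0.52 | 0.41 |
| 32 | φ = 0.5 | 0.39 | 0.70 | 0.54 |
| 32 | gains only | 0.37 | 0.91 | 0.64 |
| 40 | φ = 0.3 | 0.50 | 0.62 | 0.53 |
| 40 | φ = 0.5 | 0.49 | 0.80 | 0.69 |
| 40 | gains only | 0.48 | 0.97 | 0.84 |

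The loss grows with the correlation. At φ = 0.3 and 32 pairs, exact McNemar has no power advantage over Pearson; at φ = 0.5 and above the gap is clear.

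**The case against.** The strongest defence is that the text does not say what it is accused of. It names χ² without a variant, and McNemar's statistic is also referred to a χ² distribution. It does not mention ACP in that sentence, and it covers categorical variables generally, including comparisons of independent groups such as completers and drop-outs, where Pearson's test is right. This stands in part: applying an independent-samples test to ACP is the natural reading, not a stated plan. But an unqualified χ² beside two tests that are explicitly paired ordinarily means Pearson's, and no other test is assigned to ACP. If McNemar was meant, one word would settle it.

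The second defence is weight. ACP is a secondary outcome of a pilot, the sample size does not rest on it, and Box 1 asks only that changes in secondary outcomes be assessed. Under positive correlation the error is conservative, so it does not create false positives. All of this stands and limits the severity.

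A reader might go further in two ways that the document does not support. One is that χ² would be run on the T0-by-T2 cross-table and persistence mistaken for change; nothing in the article proposes that analysis. The other is that documents accumulate without training, so that any rise is uninterpretable. That concerns the lack of a control group, not the choice of test. The single-arm design is acknowledged under Limitations, and the article gives no background rate from which to size such a drift. A paired test would not cure it.

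**Conclusion.** The point holds with moderate weight. As ordinarily read, section 2.3.1 leaves within-resident binary change to a test for independent samples. The consequence is p-values that are too large and lost power for hypothesis (e). Any hospital-use comparison over time would be affected in the same way, though no hypothesis is attached to it.

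The size depends on the correlation. For a rise from 20% to 40% on 32 pairs at φ = 0.5, power is 0.39 with Pearson against 0.54 with exact McNemar and 0.70 with its asymptotic form. At φ = 0.3 the exact test gains nothing there. The conclusion rests on assumed rates and correlations, on residents' records being linkable across visits (which the planned paired t-test likewise needs for carers), and on independence between residents. It does not show that the plan would produce a false claim of benefit, and it does not touch the primary outcome.

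**What to change.** In section 2.3.1, limit χ² to comparisons of independent groups and add a sentence for binary outcomes measured at more than one visit. Exact McNemar suits T0 against T2 and T0 against T1. Alternatively, use a repeated-measures logistic model over the three visits, which also uses residents with incomplete follow-up; McNemar drops them, and residents who die or leave before T2 will have no T2 reading. Report the paired difference in proportions with its 95% confidence interval, and the numbers who gained and lost a document.

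The cost is one or two lines of analysis text. No extra participants, visits or data are needed.

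The exact test is itself conservative at this size (true level 0.5% to 2.6% in the table of true levels), so the choice between the exact and asymptotic forms should be fixed before the data are seen.
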